## Outcomes

### Assessment of trial feasibility

#### Research procedures feasibility.

Research procedures feasibility outcomes include number of individuals screened, number of individuals enrolled, time to first enrollment, time to reach enrollment milestones (25% target enrollment, 50% target enrollment, 75% target enrollment, 100% target enrollment), completeness of baseline and follow-up data, rate of participant drop-out or withdrawal, and the proportions of participants randomized to enhanced social prescribing that attended each scheduled session. Progression criteria for feasibility assessment are shown in Table 1.

**Table 1 pone.0350956.t001:** Progression criteria for feasibility assessment.

	Green	Yellow	Red
50% Enrollment	3 months	6 months	9 + months
Baseline data collection	100%	90%	50% or less
Drop out	<1	1-2 participants	N/A*
Intervention delivery	75% of participants	60% of participants	<60% of participants

• If greater than 2 participant drop outs are noted during the course of the study, the team will undertake full review of the study protocol and procedures to identify and mitigate design features that may be contributing to drop out.

#### Reach.

We will measure reach of study enrollment and reach of intervention participation. Reach of study enrollment will be measured by calculating the proportion of patients who indicated initial interest in the study (e.g., by responding to a study flyer or invitation) that enrolled in the study. We will also report the proportion of interested participants that screened eligible and reasons for ineligibility. We will report the demographic characteristics (age, sex, race/ethnicity, rurality, type of primary cancer, years since cancer diagnosis and household income) of enrolled participants to explore if participants are representative of the adult cancer survivor population and whether specific subpopulations are more easily reached, eligible and enrolled in our study.

#### Implementation.

We will measure participants’ completion and adherence to the intervention by tracking participant attendance at sessions, successful completion of various study activities in groups, interventionist-rated participant engagement and participant reported follow-up with plans developed. These data will be derived from interventionist notes as well as questions in the follow-up survey that will only be asked of those in the intervention arm of the study. We will also measure fidelity to the Enhanced Social Prescribing intervention through interventionalist field notes and fidelity checklists. Each week, connection navigators will be asked to complete fidelity checklists based on that week’s scheduled activities in the manual and take notes on what happened as scheduled, unanticipated events and other observations.

### Patient-reported Outcomes

#### Loneliness (primary outcome).

The UCLA Loneliness Scale, Version 3, consists of 20 items that ask patients to identify “how often they feel” followed by a positive or negative description of social interactions and perceptions, with participants ranking the frequency as never, rarely, sometimes and always (each item scored from 1 to 4). The scale is scored from 20–80 with 20 being the least and 80 being the most lonely. This scale was chosen over other loneliness scales since it is recommended by the PhenX toolkit [47], has been extensively validated [48], and has been used in previous loneliness intervention studies as an outcome measure [27,49]. We have successfully used this scale in our other interventional loneliness studies with targeted populations [50,51].

The UCLA Loneliness Scale captures social and emotional dimensions, such as perceived scarcities in social networks and intimate relationships, but does not address existential aspects of loneliness [52]. Existential loneliness, characterized by a deep feeling of separateness from others and the world, is reported among people in life-threatening situations [53], and is relevant to cancer survivors who experience existential questions of meaning and identity [54]. To capture this dimension, the validated 6-item Brief Scale of Existential Loneliness (B-SEL) will be used to assess existential loneliness as a distinct but complementary construct alongside the UCLA scale [55].

#### Social connection (secondary outcome).

Social connection will be measured by the Lubben Social Network Scale – 6. It is a well-validated 6-item questionnaire that asks about interaction and trust with family and friends in the past month. The scale is scored from 0 to 30 with each question asking about number of friends or family “seen or heard from at least once a month,” “at ease with that you could talk about private matters” or “close to such that you could call on them for help” on a ranked scale of 0 (none) to 5 (9 or more) [56].

#### Self-efficacy (secondary outcome).

Self-efficacy is the belief in one’s ability to cope with a broad range of stressful and challenging demands. The Generalized Self-Efficacy Scale has 10 items with questions about ability to cope and problem solve with responses ranging from 0 (not at all true) to 4 (exactly true) [57].

#### Quality of life (secondary outcome).

The European Organisation for Research and Treatment of Cancer Quality of Life Core 30 (EORTC-QOL-C30) is a validated and widely used patient-reported outcome measure in cancer research and practice. It contains 30 questions that ask about activities of daily living, symptomatology, overall health and quality of life [58].

#### Guideline concordant cancer survivorship care (exploratory outcome).

We will use participant self-report to up-to-date status for of age and sex appropriate cancer screening (breast, cervical, colorectal) consistent with U.S. Preventive Services Task Force recommended screening [59–61].

### Intervention

#### Enhanced social prescribing.

We engaged adult cancer survivors to collaboratively adapt an intervention, building on the social prescribing model and using the ADAPT-ITT framework [36]. The Enhanced Social Prescribing intervention builds on the social prescribing model and also includes psychosocial educational support and is delivered in a group setting.

The purpose of the Enhanced Social Prescribing intervention is to reduce loneliness and improve social connection. The interventionist, who we call a connection navigator, will be a trained health professional (MSW). The intervention will be a virtual (audiovisual), 9-week group with 6–9 individuals.

The group will meet for an hour weekly for 9 weeks. To accommodate different processing styles, learning speeds and relational needs, the facilitator will provide an *optional* 15-minute period following the session content for further discussion and debriefing. Group meetings will include brief psychoeducation, large group discussions, breakout sessions for more intimate discussions, activities, and skills practice. In the first meeting, the navigator will start by reviewing the purpose of the group, setting group ground rules, and introducing loneliness concepts. The first activity is called “Mapping my World” where participants will think about personally important beings, places and activities in which they used to engage, currently engage and desire to engage. In the second week, the connection navigator will meet with participants individually to develop a personalized connection plan and potentially help link participants to relevant community organizations and groups. The navigator will guide each participant in developing 1–2 goals that are SMART (specific, measurable, achievable, relevant, and time-bound), and comprised of concrete steps aligned with their own priorities.

Weeks 3–8 will take place in a group format and include check-ins regarding concrete steps taken on the connections plan since the last meeting. This will include a discussion of the various dimensions of loneliness (social, emotional and existential) and what can be done to address each of these [62]. In addition, the facilitator will guide content, reflection activities, and skills practice each week relevant to themes identified during the adaptation: self-compassion, energy budgeting and pacing, intentional disclosure of the cancer experience, learning from loss and grief, asking loved ones for what you need, and advocating for your health. These topics were selected to help participants process emotions that may act as a barrier to connection, iterate on and refine their connection goals in alignment with their values, and provide skills and tools to help achieve them. Finally in week 9, participants will develop a plan to sustain the progress on their connection plans by identifying areas deserving of more attention, refining their social connection plan and developing strategies to keep this work salient in their lives.

### Enhanced usual care

Those randomized to the usual care will receive usual care through their primary care provider. They will also be emailed or mailed a list of publicly available social support resources within 2 weeks of enrollment. This list of resources mimics a clinical provider giving patients handouts or resources in clinic. The email or mailed information sheet will include a description of loneliness and its impact. We will review the resources with our adaptation advisory groups.

### Procedure

#### Data collection and data management.

All enrollment and data collection procedures as shown in Fig 1. The overall study flow in shown in Fig 2. After completing an eligible screening survey, participants will be scheduled for an informed consent call with a research team member. Upon call completion, participants will be sent a link to a REDCap the baseline survey that includes informed consent (only baseline), a demographic survey (only baseline), the UCLA Loneliness Scale (Version 3) with 20-items [48,63], Brief Scale of Existential Loneliness Scale [55], Lubben Social Network Scale- 6 item [56], Generalized Self Efficacy Scale [57], quality of life questions [64] and questions about receipt of guideline concordant cancer survivorship care [65].

**Fig 1 pone.0350956.g001:**
[figure not shown]
Schedule of enrollment, interventions, and assessments.

**Fig 2 pone.0350956.g002:**
[figure not shown]
Study consort flow diagram.

We will collect the outcome measures from patients at 9 and 17 weeks after enrollment via REDCap survey. The research coordinator will conduct additional outreach, including telephone, text message, email, and written communication according to each participants’ preference to ensure complete data collection. Participants will receive USD 25 for completing each outcome assessment. Participants will be analyzed using an intent to treat analysis and included in primary outcomes analysis even if baseline data are missing. Missing data will be described to assess the amount, patterns, and reasons for missigness. Any variable with substantial missigness will undergo careful review before being considered as a candidate variable for future trials.

#### Trial monitoring.

The PI ([name]) is responsible for monitoring trial implementation and quality. The full team will meet weekly to review study procedures, data collection, and any potential challenges. The PI will be available for urgent or time sensitive trial quality issues by email and telephone. Co-Investigators will rotate on-call coverage for after hours emergencies.

### Data analysis

#### Types of data.

All study data will be collected directly from study participants using self-report.

### Statistical analyses

#### Feasibility.

A primary goal of this study is to assess feasibility of conducting a larger-scale study to test the effectiveness of the adapted, enhanced social prescribing intervention. We will use descriptive statistics to measure study procedure and intervention feasibility outcomes.

#### Effectiveness.

This feasibility study is not powered to establish effectiveness of the intervention. However, demonstration of the feasibility and completeness of data collection is important for future research. The analysis will encompass all randomized patients. Patients will be analyzed according to their assigned intervention group, regardless of what treatment they receive (intent to treat analysis). Descriptive statistics (mean and standard deviation) will summarize the distribution of primary (loneliness), secondary (social connection, self-efficacy, quality of life) outcomes at baseline, post-intervention, and 2-month follow up. Linear effects mixed models will be used to estimate differences between the intervention arm and control arm, and changes in outcomes over the study period. The model will include the treatment arm, post-treatment time point, and their interaction as independent variables and will stratify by clinical site. Intervention assignment is modeled as a fixed effect, and participants are included as a random effect with a random intercept to account for correlation of repeated outcome measurements within individuals.

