### Design

This feasibility study protocol is reported according to the SPIRIT 2013 and 2025 statement [37,38]. The SPIRIT checklist is provided in Supplement 1. We used the ADAPT-ITT process to conduct an intervention adaptation phase will follow with a randomized controlled trial (RCT) to test an Enhanced Social Prescribing intervention that targets loneliness in adult cancer survivors. We engaged adult cancer survivors and topical experts to adapt the intervention for a feasibility study. ADAPT-ITT is an 8-step approach to adapting existing evidence-based interventions to novel populations. The steps include: 1) Assessment, 2) Decision, 3) Administration, 4) Production, 5) Topical Experts, 6) Integration, 7) Training and 8) Testing [36]. The methods and results of the adaptation and intervention development phase will be reported separately.

Consistent with principles of hybrid implementation designs [39], this feasibility study prioritizes implementation outcomes—feasibility, acceptability, and appropriateness—while collecting preliminary clinical outcome data. Participants will be randomized on a 1:1 ratio to usual care (brochure) or Enhanced Social Prescribing (intervention). Outcome measures will be completed at baseline, 9 weeks (immediately post-intervention), and 17 weeks following study entry.

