#### Consent, Randomization, concealment of allocation, and blinding.

Interested potential participants will schedule a telephone call with the research coordinator to learn more about the study. After confirming study eligibility and sharing consent information, the research coordinator will obtain the participant’s verbal informed consent to participate in the study. Following verbal consent, participants will be sent an electronic survey via REDCap to review the full electronic consent information form and then subsequently complete the baseline survey. Participants will be required to review the electronic consent information form prior to initiating the baseline line survey. If participants prefer to, they may elect to complete the baseline survey over the phone with the research coordinator. Participants will be considered enrolled in the study upon completion of the baseline survey. After enrollment, a research coordinator responsible for enrollment and study operations but not involved in data collection or analysis will randomize them in a 1:1 ratio to either Enhanced Social Prescribing intervention or enhanced usual care using random permutated blocks [43]. Randomization will be conducted using REDCap. Procedures to ensure allocation concealment include using parallel structures in REDcap for each arm, which reduces the possibility that study personnel interacting with the database can infer treatment assignment.

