### Limitations

Several limitations exist. First, participant sample bias might occur, since the participants who agree to participate in this study may be more motivated to address loneliness than the general population. However, this is likely to bias us toward the null, given our plan for randomization. Second, this feasibility study is not intended to establish effectiveness of the intervention, and sub-group analyses are not possible with this small sample.

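### The stated effectiveness model lists no baseline loneliness score and leaves its role unclear; a common-baseline longitudinal model would gain precision at no data cost

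*Protocol article*

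**What the plan says.** The Effectiveness section states the fixed part of the model: "The model will include the treatment arm, post-treatment time point, and their interaction as independent variables and will stratify by clinical site". The random part is a participant intercept: "participants are included as a random effect with a random intercept to account for correlation of repeated outcome measurements within individuals". The models are meant to estimate arm differences "and changes in outcomes over the study period", and "The analysis will encompass all randomized patients".

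The Design section gives three measurement times: "Outcome measures will be completed at baseline, 9 weeks (immediately post-intervention), and 17 weeks following study entry". The baseline survey contains "the UCLA Loneliness Scale (Version 3) with 20-items" (Data collection and data management). Randomization comes after enrollment, and the consent and randomization section says: "Participants will be considered enrolled in the study upon completion of the baseline survey". The Data collection section nevertheless keeps participants in the primary analysis when their baseline data are absent.

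The Sample size section gives no calculation. It says that the pilot's estimates of baseline and outcome measures will be used to size the full trial.

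**The concern.** In a randomized trial, the baseline value of the outcome is usually the best single predictor of its follow-up value. Here it is collected before allocation but is absent from the listed model terms. The listed time term is the post-treatment time point. A model fitted only to weeks 9 and 17 can describe change between those two visits, but not change from study entry. The section therefore promises a quantity that its model, read literally, does not contain.

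The stake is precision. With 18 per arm, chance differences in baseline loneliness can be sizeable, and an unadjusted contrast carries part of them as noise. Intervals come out wider than the collected data allow. In addition, the stated model does not clearly deliver two quantities that help in planning an adjusted full-scale trial: the baseline-to-follow-up correlation and the adjusted residual SD.

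**Working it through.** The plan states no power or precision figure, so there is none to reproduce.

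**Inputs from the protocol article.** 36 participants, 18 per arm, 1:1 allocation; outcomes at baseline, 9 and 17 weeks; a participant random intercept, which implies equal variance and equal correlation across visits.

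**Assumption.** The baseline-to-follow-up correlation r is not given, so a range is shown. Outcome variance is set to 1.

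**Formulas.** Relative variance of the arm difference at one follow-up visit (multiply by 2/18 for the actual variance):
- Post-treatment scores only: 1.
- Baseline as an outcome row with a free arm effect, so that arm-by-time is a difference in change: 2(1 − r).
- Baseline adjusted: (1 − r²) × [1 + 1/(36 − 4)] = 1.031 × (1 − r²). The factor is the small-sample cost of estimating the slope.

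| r | Post-only | Change score | Adjusted | Adjusted ÷ change score | Post-only N matching 36 adjusted |
|---|---|---|---|---|---|
| 0.3 | 1.00 | 1.40 | 0.94 | 0.67 | 38 |
| 0.5 | 1.00 | 1.00 | 0.77 | 0.77 | 47 |
| 0.7 | 1.00 | 0.60 | 0.53 | 0.88 | 68 |
| 0.8 | 1.00 | 0.40 | 0.37 | 0.93 | 97 |

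The last column is 36 divided by the unrounded adjusted variance.

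**Interval width.** The post-only SE is sqrt(2/18) = 0.333 SD, giving a 95% half-width of 0.68 SD. With adjustment the half-width is 0.66, 0.60, 0.49 and 0.41 SD at r = 0.3, 0.5, 0.7 and 0.8.

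**Chance imbalance.** The SD of the baseline difference between arms is also sqrt(2/18) = 0.33 SD. The post-only contrast carries r times this: 0.10 SD at r = 0.3 and 0.27 SD at r = 0.8.

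**Break-even.** Adjustment beats post-only when 1.031 × (1 − r²) < 1, that is, when r exceeds about 0.17.

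**Rough simulation check** (150 simulated trials per r, Monte Carlo error about 6%, some fits with convergence warnings). SEs for post-only, baseline covariate, change-score reading and common-baseline model were 0.355, 0.316, 0.350 and 0.315 at r = 0.5, and 0.349, 0.246, 0.251 and 0.244 at r = 0.7. The common-baseline model tracks the covariate model, as the theory predicts.

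**The case against.** The strongest reply is that the document does not show baseline to be unused. The section speaks of change over the study, baseline is one of three outcome times, and the rule that keeps participants without baseline data would have little purpose if only post-treatment scores were modeled. All of this fits a random-intercept model with baseline as a repeated outcome. This stands: a reader might infer that baseline is simply discarded, but that follows only from the literal wording. It does not rescue the plan, because the free-arm contrast still has variance 2(1 − r) against about 1 − r².

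The analysis is also declared unpowered, implementation outcomes take priority, and an unadjusted comparison is unbiased, with chance imbalance already reflected in its SE. That is correct and limits the weight of the point. The detail could also sit in a fuller plan that is not shown, but the article does fix a list of model terms, and that list is what needs changing.

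Three stronger inferences are not supported:
- **The unadjusted SD is wrong for sizing the next trial.** It is a valid quantity and at most conservative. The document does not say that the model's residual SD will be passed on, and the correlation can be computed from the same data whatever model is fitted.
- **Stratifying by site contradicts the Limitations section**, which says "sub-group analyses are not possible with this small sample". Stratifying a model can mean a site term in one model; separate site analyses are not stated.
- **The change would restore people with no follow-up survey.** It would not: someone with baseline only adds essentially nothing to the arm contrast under any of these models.

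**Conclusion.** The point holds as one of clarity and precision, not of bias. The model as written lists no baseline score. On its literal reading it cannot deliver change from baseline; on the alternative reading it uses baseline inefficiently. Against post-only, adjustment reduces the variance by about 6%, 23%, 47% and 63% at r = 0.3, 0.5, 0.7 and 0.8. Against the change-score reading the reductions are about 33%, 23%, 12% and 7%.

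These figures rest on an assumed r and on equal variances across visits. Selecting participants on a loneliness screener may lower r, so the gain over post-only could be near the small end. No stated figure in the protocol is wrong. The consequence is moderate because the effectiveness analysis is preliminary, but its estimates are meant to inform the full trial.

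**What to change.** Replace the model sentence with a constrained longitudinal model:
- UCLA score at baseline, 9 and 17 weeks as responses, with categorical time.
- A common baseline mean across arms, and arm-by-time terms at 9 and 17 weeks.
- A participant random intercept, fitted by REML with a small-sample degrees-of-freedom correction.
- Site as a fixed effect in this single model.
- The same structure for the secondary scales.

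This is preferable to adding baseline as a covariate. Without imputation, a covariate model drops participants whose baseline is missing, whereas the Data collection section keeps them. The authors should also reconcile that rule with the one that makes baseline survey completion the condition of enrollment.

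Report the baseline-to-follow-up correlation and the adjusted residual SD for planning the full trial.

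The cost is analysis-plan wording only, with no new data. Estimating the adjustment costs about 3% in variance, which would be a net loss against post-only only if r were below about 0.17. Data collection is expected to run to the end of 2026, so the change can be made and dated before the primary analysis, while the biostatistician and analyst are still blinded.

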Multiple efficacious interventions exist for loneliness. A meta-analysis of interventions found efficacy in reducing loneliness through interventions that improved social skills, enhanced social support, and increased opportunities for social contact [27]. Building from the evidence and recognizing the substantial problem of loneliness on health, the 21st U.S. Surgeon General, [name], published an advisory on the loneliness epidemic that highlights three vital components of social connection: structure, function and quality [1,2]. Structure refers to the type, number and variety of relationships; function refers to the ways in which relationships serve an individual’s various needs (e.g., emotional, social and/or spiritual); and quality refers to the positive and negative aspects of relationships and interactions and how it is perceived by the individual. This model is adapted from Holt-Lunstad’s framework for understanding why social relationships are important for mental and physical health [28]. Social prescribing is a United Kingdom-based model to address loneliness [29]. In social prescribing interventions, patients are referred by general practitioners and then partner with lay and/or peer workers to develop personalized strategies to improve support and connection [30–35]. While evidence supports its’ efficacy, social prescribing has not been applied widely outside the United Kingdom and Europe [34,35]. Furthermore, it has not been tested specifically for adult cancer survivors with loneliness.

The aim of this study is to conduct a feasibility pilot randomized controlled trial to test, in adult cancer survivors who receive care in rural and rural-serving primary care practices, a loneliness intervention that draws on the principles of social prescribing. We will enroll 36 adult cancer survivors who are experiencing loneliness, and who will be randomized to either Enhanced Social Prescribing (n = 18) or usual care (n = 18). We will collect outcomes on loneliness, social connection, self-efficacy, quality of life, and quality of cancer survivorship care. Our goal is to improve overall wellness and quality of life among cancer survivors and demonstrate pilot efficacy of a novel, adapted program that may improve survivorship care outcomes.

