### Sample size calculation

Because this is a feasibility pilot study, no sample size calculations were performed. 36 participants was selected as an enrollment goal based on ensuring sufficient enrollment for at least two cohorts for the enhanced social prescribing intervention and matching enrollment to the available resources and timeline. The estimates of baseline and outcome measures from this study will be used to calculate sample size for a full-scale trial.

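### The outcome model leaves out treatment-group clustering in the intervention arm, and the plan does not say which pilot estimates will size the full trial

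*Protocol article*

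**What the plan says.** All references are to the protocol article.

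- **Delivery in the intervention arm** (Enhanced social prescribing): "The intervention will be a virtual (audiovisual), 9-week group with 6–9 individuals". The week 2 meeting with the navigator is individual; most of the rest is shared discussion, breakout work and skills practice.
- **Number of groups** (Sample size calculation): the goal of 36 was chosen partly with a view to "ensuring sufficient enrollment for at least two cohorts for the enhanced social prescribing intervention". The Introduction puts 18 participants in each arm.
- **Control arm** (Enhanced usual care): usual primary care plus a resource sheet, with no group element: "They will also be emailed or mailed a list of publicly available social support resources within 2 weeks of enrollment".
- **Model** (Effectiveness): fixed terms for arm, time point and their interaction, stratification by clinical site, and one random effect: "participants are included as a random effect with a random intercept to account for correlation of repeated outcome measurements within individuals". No term for treatment group or cohort appears.
- **Later use of the results** (Sample size calculation): "The estimates of baseline and outcome measures from this study will be used to calculate sample size for a full-scale trial". The section does not say which estimates are meant or how their imprecision will be handled.

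**The concern.** This is a partially nested design: one arm is treated in groups and the other is not. Members of a group share a navigator, a set of peers and a series of discussions. The primary outcome, loneliness, is one that the group itself could plausibly move. A participant random intercept handles repeated measurements on the same person. It does not handle correlation between people in the same group. Stratifying by site does not repair this, because a site term applies to both arms and the article does not form groups by site.

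Two things are at stake. In the pilot, the interval for the arm difference would be too short for any positive ICC. In the full trial, a sample size without a design effect would be too small. A separate weakness is that the sample size section leaves open whether the pilot's arm difference could itself become the target effect.

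**Working it through.** The plan has no power calculation to reproduce. The one figure that can be checked is the number of groups: 18/9 = 2 to 18/6 = 3, which agrees with at least two cohorts.

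**Inputs from the article:** 18 per arm, group size m = 6 to 9 in the intervention arm only, controls ungrouped. **Assumed, because the article gives neither:** group ICC of 0.02, 0.05 or 0.10, and for the full-trial example a true effect of 0.4 SD, two-sided 5% level and 80% power.

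**Step 1: effect on the standard error.** This treats the comparison as a difference in means at one follow-up time with equal variances. The ICC is that of the outcome as analysed.

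- Design effect in the intervention arm: DE = 1 + (m − 1) × ICC. In the control arm it is 1.
- Variance of the difference relative to the stated variance: (1 + DE)/2.
- True SE / stated SE = √((1 + DE)/2).
- Coverage of a nominal 95% interval = 2Φ(1.96 / SE ratio) − 1.

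| ICC | m | DE | Variance ratio | SE ratio | Coverage |
|---|---|---|---|---|---|
| 0.02 | 6 | 1.10 | 1.05 | 1.02 | 94.4% |
| 0.02 | 9 | 1.16 | 1.08 | 1.04 | 94.1% |
| 0.05 | 6 | 1.25 | 1.125 | 1.06 | 93.5% |
| 0.05 | 9 | 1.40 | 1.20 | 1.10 | 92.6% |
| 0.10 | 6 | 1.50 | 1.25 | 1.12 | 92.0% |
| 0.10 | 9 | 1.80 | 1.40 | 1.18 | 90.2% |

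A simulation of 18 against 18 (40,000 runs, pooled t-test) agrees. Type I error was 0.063 (three groups of 6) and 0.076 (two groups of 9) at ICC 0.05, and 0.079 and 0.098 at ICC 0.10. At ICC 0.01 it was 0.052–0.053, so the effect there is negligible.

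**Step 2: effect on a full trial sized without a design effect.** At 0.4 SD, n per arm = 2(1.96 + 0.842)²/0.4² = 98.1, rounded up to 99. Under 1:1 allocation the required n per arm is multiplied by (1 + DE)/2. Power if 99 is kept is Φ(0.4/√((1 + DE)/99) − 1.96).

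| ICC | Extra participants needed (m = 6 to 9) | n per arm needed | Power if 99 per arm is kept |
|---|---|---|---|
| 0.02 | 5–8% | 104–107 | 78–77% |
| 0.05 | 12.5–20% | 112–119 | 76–73% |
| 0.10 | 25–40% | 124–139 | 71–66% |

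**Step 3: what 18 per arm can estimate.** Degrees of freedom are 18 + 18 − 2 = 34.

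- Arm difference: 95% half-width = t(0.975, 34) × √(2/18) = 2.03 × 0.333 = 0.68 SD, before any allowance for clustering.
- SD: the 95% interval runs from 0.81 to 1.31 times the estimate. The one-sided 80% upper limit is √(34/χ²(0.20, 34)) = √(34/26.94) = 1.12 times the estimate.
- Group ICC: for an estimate of 0.05, the 95% interval is about −0.09 to 0.99 with two groups and −0.14 to 0.89 with three. The pilot cannot estimate it.

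**Step 4: what depends on which estimate is carried forward.** If only the pilot SD is used with a fixed target of 0.4 SD, mean real power in simulation is 78%, with a 19% chance of falling below 70%. If the pilot's arm difference becomes the target, then for true effects of 0.3–0.5 SD and a positive pilot estimate, median real power is 59–75%, and the chance of real power below 50% is 29–44%. Neither result includes clustering.

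**The case against.** The strongest case on the other side has four parts.

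1. **The pilot draws no conclusion from the arm difference.** The Effectiveness, Expected findings and Limitations sections all disclaim power or effectiveness, the Design section puts implementation outcomes first, and no criterion in Table 1 uses the arm difference. This stands, and it limits the harm within this trial. It does not remove the mismatch, because the article itself fixes the random-effects structure and the model is the one that will be reported.

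2. **The size of the problem rests on an assumed ICC.** This also stands. At 0.02 the interval is only 2–4% too narrow, and with no within-group correlation it is correct. Only the direction for a positive ICC is certain.

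3. **A reader might infer that leaving out clustering will leave the full trial seriously under-powered.** The documents do not support that. A too-narrow pilot interval does not itself reduce the next trial's sample size, and nothing says that the future calculation will omit a design effect. Even if it did, the power loss is about 2–14 points over ICC 0.02–0.10. The severe figures in Step 4 arise only if the pilot difference is used as the target. The sample size section does not say so, and since the Effectiveness section promises means and SDs, reading it as a reference to SDs is natural. On the other hand, its wording does not exclude the difference. The Introduction sets showing efficacy in the pilot as a goal, and the Dissemination section treats that as necessary for the later trial. So the text needs tightening, but no commitment to the poor choice can be read into it.

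4. **A fitted group random effect would not help.** This is correct. With two or three groups its variance cannot be estimated reliably, so the remedy should not depend on it.

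**Conclusion.** The point holds in a limited form. The stated model treats intervention participants as independent although they are treated in two or three groups. For a positive group ICC the interval for the arm difference is therefore too narrow: the true SE is about 2–4%, 6–10% or 12–18% larger than stated at ICC 0.02, 0.05 or 0.10, with coverage of about 94%, 93–94% or 90–92%. These figures rest on groups of 6–9, equal arms of 18 and an ICC that the documents do not give.

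The sample size section is a separate weakness: it should say which estimates go forward. Serious under-powering of the full trial is a conditional risk, tied to using the pilot difference as the target, and not a consequence of the omitted group term. The change is worth making before analysis, but the pilot's feasibility conclusions do not depend on it.

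**What to change.** **Effectiveness section.** Record each intervention participant's group. Acknowledge the one-sided clustering, and report the arm difference with its interval recomputed at fixed group ICCs, for example 0.02, 0.05 and 0.10, applied to the intervention arm only. Do not rely on a group variance fitted from two or three groups.

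**Sample size section.** State that the pilot will supply only:

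- the SD, with an upper confidence limit (for example 1.12 times the estimate for a one-sided 80% limit at 34 degrees of freedom);
- the correlation between baseline and follow-up;
- attrition and recruitment rates.

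Take the target difference from an important difference on the UCLA Loneliness Scale stated in advance. Apply 1 + (m − 1) × ICC to the intervention arm over an assumed ICC range. If the full trial keeps 1:1 allocation, this is the same total as multiplying both arms by (1 + DE)/2.

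**Cost.** A few sentences of wording, a little more analysis work and slightly wider reported intervals. Enrolment, randomisation and outcome assessment do not change.
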